**4. EXPERIMENTAL DESIGN AND METHODS**

**4.1 - Experimental Design**

The study will be conducted as a multicenter prospective evaluation of blunt head trauma patients undergoing computed head tomography. Participating study centers encompass a range of acute care facilities including academic trauma centers, community trauma centers and community emergency departments. Surveying a wide range of hospitals will make the study results generalizeable the majority of mild head injury victims.

The study will use an experimental design similar to that implemented in the previous study *Selective Computed Head Tomography in Blunt Trauma* (PHS Grant No. R01 HS09699). This computed tomographic derivation study is particularly important to the current proposal because it has already evaluated the use of a multicenter network needed to conduct the blunt head injury validation research. In addition, both studies use very similar methodology and protocols. Thus, the core methodology for evaluating blunt head injuries has already been tested in the derivation study. Personnel trained for the earlier study have become experienced with this methodology and can be quickly updated to the new protocols needed for the validation study. Most importantly, the derivation study demonstrates that the methodology for the current proposal is feasible and can be conducted in the clinical environment. The derivation study involved over 800 physicians, as well as a similar number of supporting technicians and nurses, working at 21 institutions, and accumulated over 600 cases per month.

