**4.2 Protocol Overview**

Emergency physicians working in affiliated study centers will collect survey data on all blunt head trauma victims undergoing computed head tomography. In stable patients, survey data will be collected prior to radiographic imaging. In unstable patients, clinicians will be expected to complete data collection without delaying patient care, whenever possible, and will formulate answers to data questions, even if not recorded, prior to radiographic review. Tomographic imaging of individual patients will be performed only after data collection is complete and a radiographic request has been issued. Radiographic requests will only be available after a complete data form has been submitted.

Information collected on each patient will include demographic information, select elements of history and physical examination and results of computed head tomography. Data from each study center will be captured and stored on a computer database for eventual concatenation with data from other centers.

All radiographic studies will be reviewed by clinical radiologists at each participating center. Injury determination and classification will be based on final radiological findings. Injury type and location will be recorded for all patients having significant head injuries. The hospital records of patients who have positive CT imaging will be reviewed to ascertain whether their injuries required neurosurgical intervention. Radiographic diagnoses and need for neurosurgical intervention will then be concatenated with survey data on a case-by-case basis to form the final study database.

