**4.3 - Methods**

**4.3.1 - Structure of the Multicenter Study and General Administration**

The Principle Investigator and core study administration will be located in the UCLA Emergency Medicine Center. A total of 4 hospitals will participate as study sites. Each participating institution will be represented by an emergency physician who will serve on the project steering committee and act as a site liaison. These individuals will be responsible for implementation of study protocols at that institution, and be responsible for obtaining a waiver from their respective institutional review boards and notifying the principle investigator of any protocol problems or other difficulties encountered during the study. Each site will also be staffed by a study coordinator who will be responsible for collecting and concatenating survey responses, assembling and transmitting data to a central repository, and performing quality assurance checks at the site.

In addition to the participating centers, there will be core personnel at UCLA who will monitor data collection from the centers, perform central concatenation of survey data and radiographic data, and perform data analyses. This core team will consist of the Principal Investigator, one project design member (co-investigator), a radiologist, one study coordinator, and a small team of research assistants. This team will be under the direct supervision of the Principal Investigator. Appendix - A details the administrative structure of the study and lists participating hospitals and representatives for each affiliated institution. The hospitals are listed as either 1- University based private hospital, 2 - Community based private hospital, or 3 - Public hospital.

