Study index numbers will be used to link radiographic results and the need for neurosurgical intervention to survey data. This can be accomplished in a manner identical to that used in our earlier studies using the following procedure. At the time a radiographic request is printed, an additional sheet is printed. The upper left corner of the sheet contains the patient’s medical record number, while the lower corner of the sheet contains the study index number. These sheets will be collected by site coordinators. By examining the upper left hand corner of each page, the coordinators will know which radiographic studies to retrieve. Once the radiographic study has been collected for a patient, the regional coordinators will place the lower right hand corner of the study sheet (containing the study index number) over the patient identifying information on the tomography report. The tomography report will then be photocopied with the study index number covering all identifying patient data, thus effectively redacting all identifying information from the tomography report. If the tomography report reveals an intracranial injury, the patient’s medical records for the associated visit will be reviewed, and the redacted tomography report will be modified by including a notation regarding the need, if any, for neurosurgical intervention. The redacted photocopies will then be forwarded to UCLA. Once the tomographic reports and need for neurosurgical intervention have been collected, redacted and photocopied, the sheets containing both patient medical record and study number will be cut in half to yield a one leaf with patient medical record number, and a separate leaf with the study index number. A mark will be placed on the leaf containing the patient medical record number of any patient requiring neurosurgical intervention. The study index numbers will be destroyed, while the medical record numbers will be retained for quality assurance reviews (see below). All sheets will be destroyed on study completion.

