Injuries such as isolated linear or basilar skull fractures, solitary small cerebral contusions, localized subarachnoid hemorrhage less than 1 mm thick, thin subdural hematomas less than 4mm thick, isolated pneumocephaly, and closed depressed skull fractures that do not violate the inner table will not be considered to be significant injuries [63]. Coincidental or congenital abnormalities will also not be considered to be significant intracranial injuries. Chronic subdural hematomas, without evidence of acute change, will be considered to be coincidental injuries and will not be considered to be significant acute injuries. Chronic subdural hematomas that exhibit any recent change, or those that are of indeterminate age, will be considered to be acute significant injuries.

Research assistants, blind to classification by the decision rule, will review the medical records of patients with positive tomographic scans to determine whether or not the patient received neurosurgical intervention. The need for neurosurgical intervention is defined as any of the following within seven days of the initial injury [63]:

1 – Death due to intracranial injury.

2 – Intubation for management or support of head injury.

3 – Craniotomy, elevation of skull fracture or intracranial pressure monitoring.

Cases involving death or intubation will be reviewed by the physician liaison to determine, on the basis of their best clinical judgment, whether there was a causal relationship between the event and the patients intracranial injury. The liaisons will be instructed to consider these events as causally related to intracranial injury unless there is compelling evidence to the contrary. Patients will not be considered to have received neurosurgical intervention if their death is clearly due to causes unrelated to their head injury, or if they were intubated solely to expedite care.

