**4.3.8.2 - Protection of Radiographic Data Integrity**

Preliminary diagnoses of "no injury" will be confirmed in two ways. First, quality assurance logs, which contain lists of significant radiological findings that were missed on preliminary reading, will be reviewed by the site liaisons during routine evaluations. Any revisions found on these surveys will be transmitted to UCLA where they will be incorporated into the study database. Second, the diagnoses of all blunt trauma patients admitted through the emergency department and discharged from the hospital during and up to three months after each study period will be searched and all intracranial injury cases identified. The charts of such patients will be reviewed to determine if the case was included in the study (using the patient number previously printed on the redacting forms), and if so, whether the case was classified as having an intracranial injury (based on whether the leaf was marked). The liaisons will notify core UCLA personnel of any cases of missed injury detected in this fashion. These cases will be reviewed by the site liaisons to determine, based on their best judgment, whether they involve protocol errors, and whether they represent a false-negative event (patient with a head injury, but “low-risk” according to the decision instrument). Site coordinators will notify core UCLA personnel of their findings. Reviews of the quality assurance logs and discharge diagnoses will be performed by the site liaisons on a bi-monthly basis.

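### The primary outcome runs seven days from injury but is read from one visit's record, with no rule for a CT-positive patient who is transferred out

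*Protocol*

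**What the plan says.** The primary outcome is the sensitivity of the instrument for patients who require neurosurgical intervention (4.3.7). Section 4.3.5.1.2 sets the window: "The need for neurosurgical intervention is defined as any of the following within seven days of the initial injury". The qualifying events are death due to intracranial injury, intubation for the head injury, and craniotomy, fracture elevation or pressure monitoring.

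Three places describe how the outcome is found:

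- Section 4.2: "The hospital records of patients who have positive CT imaging will be reviewed to ascertain whether their injuries required neurosurgical intervention".
- Section 4.3.5.1.2: blinded research assistants "will review the medical records of patients with positive tomographic scans to determine whether or not the patient received neurosurgical intervention".
- Section 4.3.4, the working procedure: when the report shows an injury, "the patient’s medical records for the associated visit will be reviewed, and the redacted tomography report will be modified by including a notation" on the need, if any, for intervention. It then says: "A mark will be placed on the leaf containing the patient medical record number of any patient requiring neurosurgical intervention". No mark or code is given for an outcome that was not observed.

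On sites, 4.1 lists community emergency departments separately from trauma centers: "Participating study centers encompass a range of acute care facilities including academic trauma centers, community trauma centers and community emergency departments". Section 4.3.1 adds: "A total of 4 hospitals will participate as study sites". The protocol does not mention transfer to another hospital or requests for outside records in the main cohort.

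**The concern.** The source in 4.3.4 is narrower than the outcome in 4.3.5.1.2. If a lesion is found at the enrolling hospital and the patient is sent elsewhere, a craniotomy, pressure monitor or death in the next days is recorded at the receiving hospital. The enrolling visit's record ends at transfer.

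The consequence depends on the instrument's label. If the patient was labelled positive, a true event drops out of the count toward 368 and is stored as a false positive. If the patient was labelled low risk, a miss is stored as a true negative. The second case matters more, because the plan's target allows no misses at 368 cases and the ten-miss stopping rule in 4.3.10.3 uses the same count. In addition, 4.1 argues that a wide range of hospitals makes the results generalizable. A site type that transferred its surgical cases would contribute few primary events to support that.

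**Working it through.** **1. Do the other procedures recover a transferred patient?**

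| Procedure | Reach | Recovers an event at a receiving hospital? |
|---|---|---|
| Incomplete records (4.3.7.1) | Deletes records with no CT report | No; the CT report exists |
| Stable and unstable patients (4.3.7.1.1, 4.3.7.1.2) | Deletes when the CT report and the neurosurgery information are missing, named together | Not clearly triggered; deletion would not recover the event in any case |
| Discharge search (4.3.8.2) | Covers "the diagnoses of all blunt trauma patients admitted through the emergency department and discharged from the hospital"; meant to confirm readings of no injury | No; it reads the study hospital's own charts |
| Screening of revisits and neurosurgical admissions (4.3.9.1) | Aimed at work-up bias | No provision for other hospitals |
| Three-month telephone survey (4.3.2.2, 4.3.3.1) | Un-imaged patients at one center | No; CT-positive patients are not called |

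The survey does ask un-imaged patients about care at another facility. The plan thus provides for outside care in that group but not among CT-positive patients.

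**2. The plan's own figure.** With no misses, the exact two-sided 95% lower limit is P_L = 0.025^(1/N). Setting P_L = 0.99 gives N = ln(0.025)/ln(0.99) = 367.04, so 368, as in 3.2. The limit at 368/368 is 0.9900. Enrolment at 1.2% prevalence is 368/0.012 = 30,667, which the plan gives as 31,000. Both figures reproduce.

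**3. Unrecorded cases labelled low risk.** Suppose 368 of 368 recorded cases are detected and h low-risk surgical cases went unrecorded after transfer. The correct result is 368/(368 + h), with these exact lower limits:

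| h | Result | Lower limit |
|---|---|---|
| 0 | 368/368 | 99.00% |
| 1 | 368/369 | 98.50% |
| 2 | 368/370 | 98.06% |
| 3 | 368/371 | 97.66% |
| 5 | 368/373 | 96.90% |

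**4. How many patients could be an h.** In the derivation study (3.1), 16 of 917 important injuries among 13,728 patients were labelled low risk. If that rate held, 31,000 patients would give 31,000 × 16/13,728 ≈ 36 such patients. The primary result depends on knowing the seven-day outcome in this small group.

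**5. Losses unrelated to the label.** If a fraction t of all surgical cases is lost whatever their label, expected sensitivity is unchanged and enrolment becomes 368/[0.012(1 − t)]. For t = 2%, 5%, 10% and 20% this is 31,293, 32,281, 34,075 and 38,334. The protocol gives no value of t. Shares of 10%, 25% or 50% of the 372 cases expected in 31,000 (31,000 × 0.012) would be 37, 93 or 186 cases. These are illustrative only: they assume equal prevalence across sites and that every surgical case at a transferring site is lost.

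**The case against.** The strongest objection is that the premise is not shown. No available text says that any of the four hospitals lacks neurosurgery. A community emergency department need not lack it, and the site list in Appendix A is not in the text available for this review. This stands, and it is why the size of the problem cannot be set.

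A reader might also infer that the protocol scores transferred patients as not needing surgery. No section says so. An abstractor could note a need documented in a transfer note or treat the item as missing. Intubation for the head injury, or death from it, before transfer already counts. A negative entry is only the likely default: the CT report is present, abstraction asks what the patient received, and only positives are marked. That the result would depend on the abstractor's choice is itself a weakness in a primary outcome.

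Sections 4.2 and 4.3.5.1.2 do not by themselves confine review to the enrolling hospital; only 4.3.4 limits it to the visit. Also, a patient admitted and then transferred may appear in the 4.3.8.2 search as a discharge, so that search is not blind to every transfer. But the chart reviewed is still the study hospital's and would not normally hold the later operation.

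Finally, none of the 16 low-risk injuries in the derivation study needed neurosurgery, so a hidden miss may be rare. Missing-outcome coding and sensitivity analyses may also sit in a SAP. Both points are fair. Neither removes the mismatch between outcome window and data source, which the protocol itself fixes.

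**Conclusion.** The concern holds as a gap in ascertainment. The protocol defines a seven-day outcome, names a source that stops at the enrolling visit, and gives no rule for a CT-positive patient who leaves by transfer, although community emergency departments are among its site types. Followed as written, an operation or death at a receiving hospital would normally go unrecorded.

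The frequency is unknown and could be zero if all four sites keep their surgical cases. Losses independent of the label do not bias sensitivity; they only delay reaching 368. The bias needs a patient who is CT-positive, labelled low risk, transferred, operated on or dead within seven days, and unrecorded. One such patient is enough to move a perfect result from a 99.0% to a 98.5% lower limit, so the target leaves no room for it. The documents do not support the stronger readings: that transfers are negative by rule, that a stated share of cases will be lost, or that community sites will contribute no primary events.

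**What to change.** 1. Reconcile 4.3.4 with 4.3.5.1.2 so that abstraction covers the full seven days from injury.
2. Record transfer for every CT-positive patient. Where obtainable, get the 4.3.5.1.2 outcome from the receiving hospital, before the step in 4.3.4 that separates the medical record number from the study number.
3. Code an outcome that cannot be obtained as unobserved, not as no intervention, and leave the patient out of TN and FP.
4. Report the number of such patients by instrument label and site type, with a worst-case sensitivity analysis that counts them as cases. The strictest bound counts only those labelled low risk, as misses, because adding those labelled positive as detected cases raises the estimate. Show primary cases by site type beside the generalizability statement.

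The cost is small: one added field, and a query for CT-positive transfers only. For scale, a site enrolling a quarter of 31,000 would have about 31,000 × 917/13,728 ÷ 4 ≈ 518 CT-positive patients in all at the derivation rate, and transfers can be no more than that. Outside records may need additions to the site waivers and the redaction procedure. The coding, the counts and the worst-case analysis need no outside records. If no site transfers such patients, the change costs almost nothing.

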**4.2 Protocol Overview**

Emergency physicians working in affiliated study centers will collect survey data on all blunt head trauma victims undergoing computed head tomography. In stable patients, survey data will be collected prior to radiographic imaging. In unstable patients, clinicians will be expected to complete data collection without delaying patient care, whenever possible, and will formulate answers to data questions, even if not recorded, prior to radiographic review. Tomographic imaging of individual patients will be performed only after data collection is complete and a radiographic request has been issued. Radiographic requests will only be available after a complete data form has been submitted.

Information collected on each patient will include demographic information, select elements of history and physical examination and results of computed head tomography. Data from each study center will be captured and stored on a computer database for eventual concatenation with data from other centers.

All radiographic studies will be reviewed by clinical radiologists at each participating center. Injury determination and classification will be based on final radiological findings. Injury type and location will be recorded for all patients having significant head injuries. The hospital records of patients who have positive CT imaging will be reviewed to ascertain whether their injuries required neurosurgical intervention. Radiographic diagnoses and need for neurosurgical intervention will then be concatenated with survey data on a case-by-case basis to form the final study database.

**4.3 - Methods**

**4.3.1 - Structure of the Multicenter Study and General Administration**

The Principle Investigator and core study administration will be located in the UCLA Emergency Medicine Center. A total of 4 hospitals will participate as study sites. Each participating institution will be represented by an emergency physician who will serve on the project steering committee and act as a site liaison. These individuals will be responsible for implementation of study protocols at that institution, and be responsible for obtaining a waiver from their respective institutional review boards and notifying the principle investigator of any protocol problems or other difficulties encountered during the study. Each site will also be staffed by a study coordinator who will be responsible for collecting and concatenating survey responses, assembling and transmitting data to a central repository, and performing quality assurance checks at the site.

In addition to the participating centers, there will be core personnel at UCLA who will monitor data collection from the centers, perform central concatenation of survey data and radiographic data, and perform data analyses. This core team will consist of the Principal Investigator, one project design member (co-investigator), a radiologist, one study coordinator, and a small team of research assistants. This team will be under the direct supervision of the Principal Investigator. Appendix - A details the administrative structure of the study and lists participating hospitals and representatives for each affiliated institution. The hospitals are listed as either 1- University based private hospital, 2 - Community based private hospital, or 3 - Public hospital.

**4.3.2 - Data Collection and X-ray Ordering**

**4.3.2.1 - Patient Entry**

Every blunt trauma victim presenting to a study center will undergo a clinical evaluation. The examining physician will determine if computed head tomography is indicated, using whatever criteria they deem appropriate. Physicians will be informed that it is not currently possible to exclude intracranial injuries in patients who present with any of the risk criteria, and they will be encouraged (but not required) to obtain radiographic imaging on any blunt head trauma victims presenting with one or more of these criteria (see Appendix - B for a sample data entry screen and listing of criteria). Conversely, the clinicians will also be informed that the criteria have yet to be proven reliable, and that imaging should be considered for any patient suspected of harboring an intracranial injury. There will be no formal requirement to obtain or exclude tomographic imaging of any patient. Physicians will be free to order or omit computed head tomography at their discretion.

Data capture will occur each time a request for computed head tomography is made. Tomographic imaging will be performed only after a computer generated radiographic request is presented to the tomography technician. Tomographic requests will not be available until the examining physician completes a full assessment and records the survey responses. This strategy assures that a complete data set will be captured on each patient prior to radiographic imaging. Several of the participating sites use computer based automated entry systems to order radiographic imaging. Previous experience reveals that these systems can be easily modified to adhere to our study protocols, including the collection and de-identification of survey data and imaging results. Because these systems are automated, they do not print imaging requests, but can be programmed to issue requests only after survey data has been entered. Our two prior studies reveal that these systems are easily configured, very reliable, and easier to maintain than standard systems using printed requests.

Because computer generated requests will be required for all emergency department head tomographs, patients who present with non-traumatic indications may be enrolled in the study. Physicians will be required to indicate the non-traumatic nature of these evaluations. To assure compliance with the methods of this proposal, clinicians will still be required to enter relevant study information. This information will be retained in a separate database, and will be analyzed separately from data on blunt head injury victims. This information may be useful in developing selective indications for non-traumatic computed head tomography. However, this information is not relevant to the hypotheses being tested in this study.

Imaging requests may be generated prior to complete data entry in physiologically unstable patients. Clinicians will ultimately complete data entry in these patients, but complete data entry may occur after computed head tomographs have been reviewed. In such cases, the data entry for the case will document the physiologic instability and non-concurrent nature of the data collection. In our previous study, clinicians classified 8.7% of patients as unstable (including 17.5% of patients with intracranial injuries), but were able to complete assessments on all patients. In this regard, the study protocol allowed clinicians to provide expeditious care to even the most severely injured patients, while having a negligible impact on data collection.

Data will be collected on all blunt head injury victims entered into the study. Inclusion will not depend on age, sex, race or ethnic origin. Specific information regarding race will be collected to determine what effect, if any, race may have in evaluating patients for risk of injury. Demographic analyses will be performed on age and sex data. Study sites (Appendix A) have been selected to represent a broad spectrum of medical environments. These sites are expected to enroll a diverse population containing all races and both sexes. All sub-populations will be represented in the study in the same proportions as they present with blunt head injuries.

